## Abstract

**Background:**

Family-based treatment is an efficacious outpatient intervention for medically stable adolescents with anorexia nervosa. Previous research suggests family-based treatment may be more effective for some families when parents and adolescents attend separate therapy sessions compared to conjoint sessions. Our service developed a novel separated model of family-based treatment, parent-focused treatment, and is undertaking a randomised controlled trial to compare parent-focused treatment to conjoint family-based treatment.

**Methods/Design:**

This randomised controlled trial will recruit 100 adolescents aged 12–18 years with DSM-IV anorexia nervosa or eating disorder not otherwise specified (anorexia nervosa type). The trial commenced in 2010 and is expected to be completed in 2015. Participants are recruited from the Royal Children’s Hospital Eating Disorders Program, Melbourne, Australia. Following a multidisciplinary intake assessment, eligible families who provide written informed consent are randomly allocated to either parent-focused treatment or conjoint family-based treatment. In parent-focused treatment, the adolescent sees a clinical nurse consultant and the parents see a trained mental health clinician. In conjoint family-based treatment, the whole family attends sessions with the mental health clinician. Both groups receive 18 treatment sessions over 6 months and regular medical monitoring by a paediatrician. The primary outcome is remission at end of treatment and 6 and 12 month follow up, with remission defined as being ≥ 95% expected body weight and having an eating disorder symptom score within one standard deviation of community norms. The secondary outcomes include partial remission and changes in eating pathology, depressive symptoms and self-esteem. Moderating and mediating factors will also be explored.

**Discussion:**

This will be first randomised controlled trial of a parent-focused model of family-based treatment of adolescent anorexia nervosa. If found to be efficacious, parent-focused treatment will offer an alternative approach for clinicians who treat adolescents with anorexia nervosa.

**Trial registration:**

Australian and New Zealand Clinical Trials Registry ACTRN12610000216011.

## Background

Anorexia nervosa (AN) is an eating disorder characterised by restricted dietary intake leading to low body weight, a fear of weight gain, and disturbed body image [1]. The highest incidence of AN is during adolescence [2], with 1.1% of adolescents having a lifetime history of AN or subthreshold AN (i.e., eating disorder not elsewhere classified; DSM-IV EDNOS) [3]. AN has a significantly detrimental impact on physical and psychological functioning, including having the highest mortality rate of all psychiatric conditions [2]. Current evidence supports family-based treatment (FBT) as an efficacious outpatient intervention for medically stable adolescents with AN [4-8]. Our research compares a parent-focused model of FBT in which parents and adolescents attend treatment sessions separately to a standard conjoint model.

FBT is a manualised outpatient treatment in which a mental health clinician assists parents to actively support weight gain and normalise eating patterns for their adolescent [9]. Treatment initially focuses on weight restoration. Parents are required to take control of meals, support their adolescent to eat, and prevent compensatory behaviours. Once weight is restored and resistance lowered, control of eating is returned to the adolescent and developmental issues can be addressed. Traditionally, FBT is delivered in a conjoint model whereby the whole family is seen together by the therapist (hereafter referred to as conjoint family-based treatment; CFT). While CFT allows the therapist to directly observe and intervene in family interactions, it also raises many challenges. For example, the content of sessions may not be suitable for all family members at all times, and some parents may be critical of their adolescent or display distress which impacts negatively on their adolescent [6,10,11]. The adolescent’s illness may also manifest in behaviours which interfere with the therapeutic process between the parents and therapist. In addition, there are practical issues that may prevent family members attending sessions together (e.g., work, school, travel) or that impede therapists being able to accommodate whole families (e.g., small office space) [12]. The CFT model also poses a challenge for dissemination of FBT, in that therapists without formal training in general family therapy are at times reluctant to treat within a conjoint format that includes patient, parents, other caregivers, and siblings. Of particular concern is the second session of FBT, an in-vivo family meal in which the therapist must facilitate parental efforts in the nutritional rehabilitation of their ill child, while mobilising the siblings to take on a supportive role. The success of this powerful session is one hypothesised mechanism of FBT, but no dismantling studies demonstrating its unique contribution to treatment outcomes have been conducted.

Separated models of FBT in which the adolescent and parents are seen in separate individual sessions can overcome many of the difficulties of CFT, may be just as effective as CFT, and may even be better suited to some families. In the earliest randomised controlled trial of separated family therapy (SFT) [5], 18 adolescents with AN received either CFT or a SFT model in which the therapist spent part of the session with the adolescent alone and part of the session with the parents alone. Both groups had a significant increase in weight, but although there was a somewhat greater increase in the SFT group (+19.9% expected body weight, EBW) compared to the CFT group (+13.2% EBW), group differences were not significant. In a subsequent larger trial, 40 adolescents with AN were randomised to CFT or SFT [6]. Using Morgan-Russell outcome criteria [13], 76% of the SFT group had good or intermediate outcome at end of treatment compared to 47% of the CFT group, with outcomes improving further at 5-years follow-up (SFT = 90% and CFT = 78% good/intermediate outcome) [11]. Once again, however, the group differences were not statistically significant. Of importance, in both trials there was evidence that adolescents from critical families (i.e., those with high expressed emotion) had poorer outcome in CFT than in SFT [5,6,11].

While the sample size of these studies limits the interpretation of their findings, they provide preliminary indications that SFT produces similar, and potentially superior, outcomes to CFT. They further suggest that, at least for some families, SFT may be uniquely clinically indicated. For the current study, we amplified the differences between CFT and SFT to develop a separated model of treatment in which the therapist sees only the parents in treatment sessions while a nurse attends to the monitoring of the adolescent’s weight, mental and medical status and plays a supportive role. By extension, there is no family meal session in this model. Unlike CFT and previous separated models of FBT, in this treatment parents are for the most part the exclusive participants in therapy, similar to other parent training-based psychological interventions [14]. Hence, the therapy was named parent-focused treatment (PFT). The structure of PFT is described in the Methods section.

### Aims and hypotheses

The aims of this study are to:

1. Examine the relative benefits of PFT compared to CFT in a randomised controlled trial with a cohort of outpatients with AN and EDNOS- Anorexia Nervosa type (EDNOS-AN);

2. Explore predictors and moderators of treatment response; and

3. Explore mediators of treatment response.

It is hypothesised that:

1. PFT will be more effective than CFT as indicated by more participants achieving full remission and partial remission after 6 months of treatment and at 6 and 12 months follow-up;

2. Adolescents with parents who are highly critical and are assigned to PFT will have better outcomes compared to adolescents with parents who are highly critical and are assigned to CFT;

3. Regardless of treatment assignment, outcomes will be poorer for adolescents with co-morbid psychiatric illness, high levels of obsessionality, features of personality disturbance, parent psychopathology, high levels of parental criticism, poor therapeutic relationship, and/or low expectation for treatment effectiveness. These factors will also be explored as potential moderators of outcomes with respect to treatment assignment;

4. Treatment response will be mediated by reduced dietary restraint and depressive symptomatology, and increased self-esteem, parent efficacy and family functioning.

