### Randomisation

A statistician independent of the research group generated a randomisation schedule using block randomisation with variable block sizes (currently masked from research personnel). Randomisation is stratified by eating disorder severity (low vs. high) to ensure equal allocation to each of the treatment arms. High severity is defined as <80% EBW, illness duration >12 months, and the presence of one other psychiatric diagnosis (i.e., all three criteria must be met). The randomisation schedule is only accessible by designated staff members at the Royal Children’s Hospital who are independent of the Eating Disorders Program team including the research team. When randomisation is required, a researcher sends an email with the participant identification number and severity category to one of the independent staff members requesting randomisation. The allocation is sent via reply email and the researcher communicates the allocation to the family and treating clinicians.

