### Interventions

All participants, regardless of treatment group, receive 18 therapy sessions over 6 months. The frequency of sessions is the same across treatment groups: twice weekly in weeks 1 and 2, weekly for weeks 3 to 10, fortnightly for weeks 11 through 18, and every third week for weeks 19 to 24. In other words, dose and intensity of treatment are the same for CFT and PFT.

*Conjoint Family-Based Treatment (CFT)*. In CFT, the whole family is expected to attend treatment sessions. This includes the adolescent, both parents (for two-parent families), and siblings. Treatment progresses through three phases detailed in the treatment manual [9]. In the first phase (sessions 1–12), therapy is focused on the eating disorder and includes a family meal undertaken in session two. This phase is characterised by attempts to absolve the parents from the responsibility of causing the disorder, and by capitalising on the strengths of their parenting to facilitate their offspring’s nutritional rehabilitation. Families are encouraged to work out for themselves how best to restore their child’s weight, drawing on a combination of common-sense practices (i.e., FBT asks parents, “What would you be feeding your child now if s/he were underweight for a medical reason?” and cautions them against symptom accommodation) and the eating disorders expertise of the therapist. In Phase 1, the majority of weight restoration is accomplished. In Phase 2 (sessions 13–16), once weight restoration is nearing completion, parents are helped to transition eating and weight control back to the adolescent in a developmentally appropriate manner. The third phase (sessions 17–18) is initiated when the patient achieves a stable weight and self-starvation has abated. The central theme is the establishment of a healthy adolescent stage of development in all aspects of functioning, including the patient’s relationship with his or her parents. In CFT, the mental health clinician weighs the patient at the beginning of each session and spends approximately 10 minutes with the adolescent before bringing the rest of the family in for the remainder of the 50-minute session.

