### Measures

The study assessment timeline is shown in Table 1. The assessments are part of routine care of all patients in FBT at the service. Face-to-face assessments are conducted at baseline, week 4, week 12, end of treatment (i.e., Week 24), and at 6 and 12 months post-treatment completion. Written questionnaires are completed at each of these face-to-face assessments and at fortnightly intervals during the first 12 weeks of treatment. As a token of appreciation and reimbursement for time and travel, parents and adolescents receive a $20 gift card for attending each assessment at mid-treatment, end-of-treatment and follow-up. Participants who complete all written questionnaires are entered into a yearly draw for a $100 gift card.

**Table 1 T1:** Study measures and time points

**Measure**	**Source**	**Baseline**	**Each treatment session**	**Week 1**	**Week 2**	**Week 4**	**Weeks 6, 8 & 10**	**Week 12**	**Week 24 (End of Treatment)**	**6mth & 12mth FU**
Weight	Adolescent	✓	✓			✓		✓	✓	✓
Height	Adolescent	✓						✓	✓	✓
Menstrual status	Adolescent	✓	✓					✓	✓	✓
Binge/purge frequency	Adolescent	✓	✓			✓		✓	✓	✓
Eating Disorder Examination	Adolescent	✓						✓	✓	✓
	Parent	✓						✓	✓	✓
Mini International Neuropsychiatric Interview	Adolescent	✓							✓	✓
	Parent	✓							✓	✓
Children’s Yale-Brown Obsessive Compulsive Scale	Adolescent	✓				✓		✓	✓	✓
Yale-Brown-Cornell Eating Disorder Scale	Adolescent	✓				✓		✓	✓	✓
Five Minute Speech Sample	Parent	✓				✓		✓	✓	✓
Symptom Checklist-90-R	Parent	✓								
Family Environment Scale	Adolescent	✓			✓	✓	✓	✓	✓	✓
	Parent	✓			✓	✓	✓	✓	✓	✓
Borderline Personality Questionnaire	Adolescent	✓						✓	✓	✓
Children’s Depression Inventory	Adolescent	✓			✓	✓	✓	✓	✓	✓
Rosenberg Self-Esteem Scale	Adolescent	✓			✓	✓	✓	✓	✓	✓
Eating Disorders Examination-Questionnaire	Adolescent	✓			✓	✓	✓	✓	✓	✓
Positive and Negative Affect Scale	Adolescent	✓			✓	✓	✓	✓	✓	✓
	Parent	✓			✓	✓	✓	✓	✓	✓
Parents Versus Anorexia Scale	Parent	✓			✓	✓	✓	✓	✓	✓
Therapy Suitability and Patient Expectancy	Adolescent			✓	✓	✓	✓	✓	✓	
	Parent			✓	✓	✓	✓	✓	✓	
Helping Relationship Questionnaire	Adolescent				✓	✓	✓	✓	✓	
	Parent				✓	✓	✓	✓	✓	

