*Parents Versus Anorexia Scale (PVA)*[55]. This is a 7-item measure of self-efficacy of parents in FBT; that is, parents’ perceptions of their ability to bring about recovery in their child [55]. The measure was designed to align with the principles of FBT outlined in the manual [9]. The PVA has been found to have acceptable internal consistency and to be positively correlated with total increase in % EBW during FBT [55].

*Therapy Suitability and Patient Expectancy*[56]*.* Parent and adolescent perception of the suitability of the treatment is assessed with the question “How suitable do you think this therapy is for your problem?” Their expectation of improvement with treatment is assessed with the question “How successful do you think therapy will be?” Each item is rated on an 11-point scale (0 = *Not at all*, 10 = *Extremely*). The questions were adapted from those used in a trial of FBT for bulimia nervosa [56].

*Helping Relationship Questionnaire (HRQ)*[57]. The HRQ measures two main aspects of the therapeutic relationship: the experience of being helped and supported, and the experience of being in a collaborative effort with the therapist. Eleven items are rated on a 6-point scale (-3 = *Strongly feel it’s true*, +3 *Strongly feels it’s untrue*). Two additional open-ended questions ask the respondent to comment on the ways they feel improved and the ways they feel worse, and a final item asks the respondent to rate their improvement so far (1 = *Not at all*, 5 = *Very much*). The HRQ has been used in a trial of FBT for bulimia nervosa [56].

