### Data analysis

Remission will be determined separately at post-treatment and follow-up. The primary outcome analysis will be based upon intent-to-treat. In those cases in which there are missing post-treatment or follow-up data, the pre-treatment observation will be carried forward to characterise that participant’s response [58]. Groups will be compared on remission at post-treatment and follow-up using two-tailed Fisher’s Exact test with *alpha* set to .05. The secondary outcome category is the proportion of participants partially remitted. CFT and PFT will be compared at post-treatment and follow-up using Fisher’s Exact test.

A secondary analysis will be performed using a mixed effects linear regression model [59] to compare CFT and PFT participants on eating pathology, depression and self-esteem at mid-treatment (week 12), end-of-treatment (week 24), 6-month follow-up, and 12-month follow-up controlling for pre-treatment levels. Analyses will be performed on log-transformed variables for behavioural frequencies to satisfy the assumptions for the linear model. Random regression models allow for the inclusion of individuals with missing data. Consequently, no data imputation will be performed. Comparisons between groups will be based upon the main effect for group with a two-tailed alpha of .05. *Post hoc* comparisons between groups at specific time-points will be based upon a two-tailed Bonferroni corrected *Post hoc* comparisons between groups at specific time-points will be based upon a two-tailed Bonferroni corrected *alpha* of .0125 (.05/4).

Moderation analyses will be performed using logistic regression analyses, with models using main effects for treatment, moderator, and treatment-by-moderator analyses to predict remission at post-treatment and follow-up assessments. Bootstrap mediation analyses with bias-corrected confidence intervals will be performed using the *PROCESS* macro developed by Hayes [60].

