## Discussion

This trial will be the largest randomised trial of a separated model of FBT for adolescents with AN to date. If found to be efficacious, PFT has the potential to increase recovery rates by offering clinicians and families an alternative approach to standard conjoint FBT.

Although standard FBT has the most promising evidence-base for treatment of adolescent AN [61,62], it has significant limitations. As described earlier, the standard conjoint format described in the manual (i.e., CFT) [9] raises many challenges and is difficult for many families and therapists to adhere to for a variety of reasons [12,19]. Moreover, studies using strict outcome criteria suggest CFT only achieves remission in around 50% of adolescents [6,8]. As individual therapies are generally found to be less effective in this population [8,63], clinicians and researchers tend to focus on improving outcomes by modifying FBT. This trial builds on two previous studies that indicated restructuring FBT with parents and adolescents attending separate sessions may be an efficacious alternative treatment for some families.

Of importance, the trial will not only indicate whether PFT is a more efficacious alternative to CFT, but moderator analyses will indicate whether there are specific patient or family characteristic that are useful in guiding the selection of treatment approach. For example, previous research suggests highly critical families may be better suited to SFT rather than CFT [5,6] and that adolescents with high eating-related obessionality are better suited to CFT than adolescent-focused therapy [64]. Furthermore, mediation analyses in this trial will indicate potential mechanisms of action which could be the target of future efforts to enhance FBT. For example, if remission is shown to be mediated by improved parent efficacy, techniques could be integrated into FBT to increase efficacy in parents who struggle with this during treatment.

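### Expectancy and therapeutic relationship are listed as moderators but are first measured after the family knows its arm, so their treatment-by-moderator tests cannot show who should receive which treatment

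*Protocol article*

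**What the plan says.** **The moderators.** Hypothesis 3 (Aims and hypotheses) lists seven factors expected to predict poorer outcome in either arm. The last two are "poor therapeutic relationship, and/or low expectation for treatment effectiveness. These factors will also be explored as potential moderators of outcomes" with respect to treatment assignment.

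**The measurement.** In Table 1 (Measures) the row "Therapy Suitability and Patient Expectancy" has empty baseline cells for adolescent and parent, and its first tick is week 1. The Helping Relationship Questionnaire starts at week 2. The expectancy item reads "How successful do you think therapy will be", and the companion item asks how suitable the present therapy is.

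**Knowledge of the arm.** Under Randomisation, "the researcher communicates the allocation to the family and treating clinicians". Under Interventions, sessions run "twice weekly in weeks 1 and 2, weekly for weeks 3 to 10".

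**The model.** Data analysis specifies logistic regression "with models using main effects for treatment, moderator, and treatment-by-moderator analyses to predict remission at post-treatment and follow-up assessments". It does not limit moderators to pre-randomisation measures.

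**The intended use.** The Discussion says that "moderator analyses will indicate whether there are specific patient or family characteristic that are useful in guiding the selection of treatment approach".

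**The concern.** A moderator is useful for choosing between two treatments only if it can be known before the choice and is not itself altered by the choice. A rating given after the family has learned its arm fails on both counts. It is an opinion of the allocated therapy, so a family in one arm and the same family in the other could give different answers.

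Two things then go wrong in the planned model. Low raters in one arm are not the same kind of family as low raters in the other, so the treatment term no longer compares like with like. And if the rating reflects prognosis more closely in one arm, the interaction term picks up that difference even when the treatments work equally well for everyone.

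At stake is a conclusion such as low-expectancy families doing better in one arm. The data could not support it, and a clinician could not apply it before allocation.

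**Working it through.** **1. Timing of each hypothesis 3 factor (Table 1).**

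| Factor | Measure | First measured |
|---|---|---|
| Comorbid psychiatric illness | MINI-Kid | Baseline |
| Obsessionality | CY-BOCS, YBC-EDS | Baseline |
| Personality features | BPQ | Baseline |
| Parent psychopathology | SCL-90-R | Baseline |
| Parental criticism | FMSS | Baseline |
| Expectation of treatment | Suitability and expectancy items | Week 1 |
| Therapeutic relationship | HRQ | Week 2 |

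Five of the seven have a baseline value and two do not. The baseline assessment belongs to intake. Consent, randomisation and disclosure of the arm come after it.

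**2. What conditioning on the later rating does.** The protocol gives no effect sizes, so everything in this step is assumed. Let T be the arm, Y remission, U latent prognosis (mean 0, SD 1) and M the rating. The true model has no treatment effect and no moderation:

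logit P(Y=1) = s·U, with s = 1.0 or 1.5

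The rating is M = r·U + √(1−r²)·e + d·T, where r may differ by arm, e is standard normal noise and d is the shift caused by the arm. The fitted model is the protocol's:

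logit P(Y=1) = β0 + β1·T + β2·M + β3·T·M

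Given M and T, the mean of U is r·(M − d·T). Before the shrinkage caused by the unexplained part of U, two results follow:

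- The slope on M is about s·r in each arm, so β3 is about s·(difference in r). With s = 1.0 and r = 0.6 versus 0.2, that is 0.4 although no moderation exists.
- With equal r, β3 is zero but β1 is about −s·r·d. With d = 0.5 this runs from −1.0×0.4×0.5 = −0.20 (r = 0.4) to −1.5×0.6×0.5 = −0.45 (r = 0.6), although the true effect is zero.

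**3. Simulation at the planned size** (50 per arm, Wald test at 0.05; ranges cover s = 1.0 and 1.5):

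| Relation of rating to prognosis | False interactions |
|---|---|
| Equal in both arms, no shift | 5% |
| Equal in both arms, 0.5 SD shift by arm | about 5% |
| r = 0.5 vs 0.3 | 7-8% |
| r = 0.6 vs 0.2 | 13-20% |
| r = 0.6 vs 0 | 23-36% |

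With the 0.5 SD shift and r from 0.4 to 0.6, the null treatment effect appears as a log-odds of about −0.16 to −0.37, that is odds ratios of exp(−0.16) = 0.85 to exp(−0.37) = 0.69. These sit below the unshrunken −0.20 to −0.45 in size, as expected.

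**4. A milder set of assumptions.** Here expectancy itself carries a log-odds of 0.5 and prognosis 1.0.

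- Pre-randomisation expectancy: interaction near zero, 4.5% rejections.
- Rating shifted by 0.5 SD in one arm: interaction near zero, treatment coefficient −0.22.
- Rating loading on prognosis at 1.0 in one arm and 0.2 in the other: interaction −0.15, 6.5% rejections.

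**The case against.** The case on the other side is substantial.

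- **The analysis is exploratory.** Aim 2 is to explore predictors and moderators, and hypothesis 3 first concerns prediction whatever the arm. An early rating can serve that purpose. This stands: use as an early predictor remains open.
- **The main results do not depend on it.** Remission is compared by Fisher's exact test, and nothing in the protocol reads the treatment effect from a moderator model. Hypothesis 2 uses parental criticism, which has a baseline measure. This stands. A reader might infer that the trial's efficacy conclusion is at risk, and the protocol gives no support for that.
- **Treatment may not have begun at the first rating.** Week 1 contains two sessions, so a reader might infer that the first expectancy form follows the start of therapy. Table 1 does not say whether it precedes the first session. The point needs only that the arm is known, which the Randomisation section documents.
- **Knowing the arm does not by itself inflate false interactions.** This also stands. A pure shift leaves the rate at about 5%. Inflation requires the rating to track prognosis differently by arm, and the documents give no evidence on that. Without rescaling the noise to unit variance, the rates fall to 8-12% for 0.6 versus 0.2 and 5-7% for 0.5 versus 0.3.
- **The Discussion's examples are criticism and obsessionality.** Both are measured at baseline, so its claim about guiding treatment selection should not be read as a specific promise about expectancy. However, the general claim is made for the moderator analyses, and hypothesis 3 places these two factors among them.
- **Therapeutic relationship cannot exist before therapy.** So week 2 is not a scheduling error. The fault lies in calling it a moderator.

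**Conclusion.** The point holds on the text alone. The protocol names two factors as moderators by treatment assignment and schedules their first measurement after the arm is disclosed. It sets no rule limiting the interaction model to earlier measures. Followed as written, it conditions on post-randomisation variables, and the results cannot say who, before allocation, would do better in which arm. An analysis plan could relabel these variables but could not supply a baseline value that was never scheduled.

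The numerical distortion is uncertain. Under the assumptions shown, false interactions range from the nominal 5% to 36%, and the upper figures need a large difference between arms in how the rating relates to prognosis. The failure of interpretation does not depend on those assumptions. It is confined to two of seven exploratory moderators, and is worth correcting because the correction is nearly free.

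**What to change.** In Data analysis, state that moderators are restricted to factors measured before randomisation: comorbidity, obsessionality, personality features, parent psychopathology and parental criticism. In hypothesis 3, take expectancy and therapeutic relationship out of the moderator sentence and describe them as early predictors of outcome or as post-allocation process variables.

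This costs one sentence in the analysis text and a small edit to the hypothesis. No data are lost. The downside is that expectancy cannot be tested as a moderator in this trial.

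Adding expectancy items at baseline for the remaining recruits is not recommended as the remedy. Recruitment was due to end around July 2014 and the article already reports assessments to January 2014, so few families would contribute. A question asked before allocation would also measure something different from the present rating of the allocated therapy, and could not be pooled with it.

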*Parent-Focused Treatment (PFT).* In PFT, treatment progresses through the same three phases as CFT [9], however the parents and adolescent are seen in separate sessions. Each appointment begins with the adolescent being seen by the clinical nurse consultant who weighs the adolescent, assesses medical stability as needed, and provides brief supportive counselling for up to 15 minutes. The nurse communicates the weight and any other pertinent information to the therapist who then sees the parents for 50 minutes. The focus and content of the parent sessions are the same as in CFT, but without direct interaction with the adolescent. The only direct contact between the therapist and adolescent is at the first session, when the therapist briefly introduces themselves, and at the end of the final session, when the therapist farewells the family. As noted above, there is no family meal in PFT. Siblings are not included in PFT treatment sessions but other caregivers involved in weight restoration can be included (e.g., grandparent). A study treatment manual was developed for PFT and a detailed description of PFT will soon be published [19].

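### Two of the seven listed moderators, therapeutic relationship and treatment expectation, are measured only after allocation and cannot serve as moderators

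*Protocol article*

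**What the plan says.** All references are to the protocol article.

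- **Aims and hypotheses, hypothesis 3.** The list of factors ends with "poor therapeutic relationship, and/or low expectation for treatment effectiveness". The next sentence reads "These factors will also be explored as potential moderators of outcomes with respect to treatment assignment", and no factor is excepted.
- **Measures, Table 1.** The row "Therapy Suitability and Patient Expectancy" has an empty baseline cell and its first tick at Week 1. The row "Helping Relationship Questionnaire" has empty baseline and Week 1 cells and its first tick at Week 2. Both hold for adolescents and parents.
- **Randomisation.** Once the allocation is returned, "the researcher communicates the allocation to the family and treating clinicians".
- **Interventions, PFT.** "The only direct contact between the therapist and adolescent is at the first session", apart from a farewell at the end of the last one.
- **Data analysis.** The logistic models contain treatment, moderator and "treatment-by-moderator analyses to predict remission at post-treatment and follow-up assessments".
- **Discussion.** Moderator analyses are meant to identify patient or family characteristics that help in selecting a treatment.

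For the secondary point, hypothesis 4 states "Treatment response will be mediated by reduced dietary restraint and depressive symptomatology". Under Measures, the dedicated restraint instrument is the self-report EDE-Q Restraint subscale, described as closely matching the EDE interview. Full remission requires at least 95% EBW together with an EDE Global score near community norms.

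**The concern.** A moderator answers the question of which patients do better on which treatment, so it has to be a characteristic that the allocated treatment cannot have altered. A rating first taken once the family knows its arm, and for the relationship scale after sessions have begun, is partly a consequence of treatment. Its interaction with treatment mixes three things: real effect modification, the effect of the arm on the rating, and any difference between arms in what the rating reflects.

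The last of these is a particular risk for the adolescent relationship score. The questionnaire concerns help from, and collaboration with, the therapist. In CFT the adolescent meets the therapist at every session; in PFT, almost never. Expectancy has its own difficulty: the items ask about the therapy being received, so respondents in the two arms are rating different treatments.

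At stake is the treatment-selection message. Neither rating exists when the choice of treatment has to be made, so even a genuine association could not guide it.

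**Working it through.** **1. Timing of each factor in hypothesis 3 (Table 1)**

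| Factor | Instrument | Baseline value? |
|---|---|---|
| Psychiatric comorbidity | MINI-Kid | yes |
| Obsessionality | CY-BOCS, YBC-EDS | yes |
| Personality disturbance | BPQ | yes |
| Parent psychopathology | SCL-90-R | yes |
| Parental criticism | FMSS | yes |
| Treatment expectation | expectancy items | no, first at Week 1 |
| Therapeutic relationship | HRQ | no, first at Week 2 |

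Five of seven have a baseline measure. Under Interventions, weeks 1 and 2 are treatment weeks with two sessions each. On schedule, the first HRQ therefore follows at least two sessions. For expectancy, only disclosure of allocation is certain to come first; the article does not say whether the Week 1 form precedes session 1.

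**2. Can this produce a false interaction?**

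The plan gives no figure for the moderator analyses. Its enrolled size is reproduced as 45/(1 − 0.10) = 50 per arm, and that size is used here. Everything else is assumed:

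- Prognosis U is standard normal, and logit P(remission) = −0.1 + t·T + 1.0·U, with T = 1 for PFT and t = 0 or 1.2. There is no moderation in this model.
- Post-allocation rating M = b·U + 0.5·T + √(1 − b²)·noise, where b may differ by arm.
- Baseline comparator: the same b = .6 in both arms and no shift.
- Analysis: logistic regression on T, M and T×M, two-sided 5% test of T×M, 2,000 simulated trials per setting.

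| Rating | False interaction, t = 0 | False interaction, t = 1.2 | Median T×M coefficient (t = 0; 1.2) |
|---|---|---|---|
| Baseline moderator, b = .6 | 4.7% | 5.0% | −0.03; 0.03 |
| Post-allocation, b = .6 in both arms (mean shift only) | 4.4% | 4.9% | −0.01; 0.02 |
| b = .6 CFT, .3 PFT | 9.8% | 9.1% | −0.30; −0.30 |
| b = .6 CFT, .1 PFT | 17.7% | 17.0% | −0.48; −0.48 |
| b = .7 CFT, 0 PFT | 31.2% | 29.8% | −0.64; −0.70 |

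The simulation error (one standard error) is √(.05 × .95/2000) = 0.5 points near 5% and √(.3 × .7/2000) = 1.0 point near 30%.

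A hand check explains the coefficients. M has unit variance within each arm, so the expected U given M changes by b per unit of M, and the slope of M is roughly b × 1.0. The slope difference is then about .3 − .6 = −0.3, .1 − .6 = −0.5 and 0 − .7 = −0.7, close to the simulated values. The interaction comes entirely from the rating carrying different information in the two arms.

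**3. Restraint mediator (secondary)**

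Assumptions:

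- EDE Global is the mean of its four subscales, which intercorrelate at .6.
- EDE-Q Restraint correlates .7 or .9 with the EDE Restraint subscale and is taken at the same visit as the outcome.
- The weight criterion is met independently of the EDE, with probability .75.
- Treatment lowers all four subscales equally, and restraint causes nothing.

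With N = 100, 150 trials per setting and 200 bias-corrected bootstrap resamples each, mediation was declared as follows (range over the two correlations):

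| Arm effect on each subscale | Mediation declared |
|---|---|
| none | 4–9% |
| 0.3 SD | 9–29% |
| 0.5 SD | 38–64% |
| 0.8 SD | 55–78% |

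The simulation error is up to √(.25/150) = 4 points. The overlap misleads only when the arms truly differ on the EDE.

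**The case against.** The strongest replies, and what stands of each:

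- **The analyses are exploratory and say so.** True, and the primary Fisher comparison and the mixed models do not depend on them. The label does not make a post-allocation rating a moderator, however, and the list makes no exception.
- **The Discussion's examples of moderators are parental criticism and eating-related obsessionality, both measured at baseline.** This stands and narrows the consequence: the disputed variables are not singled out there for treatment selection. They remain on the list that feeds that purpose.
- **Inflation is not inevitable.** This stands. When the arm only shifts the mean rating, the false-positive rate stays at about 5%. The argument for unequal tracking is also specific to the adolescent relationship score, since parents see the therapist in both arms. For parent ratings and expectancy, the objection rests on timing and interpretation, and no error rate was calculated for expectancy.
- **Restraint and remission use different instruments.** This stands. A reader might infer that the mediator is itself part of the outcome. The documents do not support that: the restraint-only scale is the EDE-Q questionnaire, remission uses the EDE interview plus a weight criterion, and the article gives no formula for the Global score. What remains is overlap in content.

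A reader might also fault the timing of the mediators or the lack of a multiplicity adjustment across the interaction tests. The EDE-Q is collected repeatedly up to Week 12, so temporal order is available. Choice of visit and error control for exploratory tests can be left to an analysis plan, so neither is a fault in this article.

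**Conclusion.** The point holds for the moderator list. Hypothesis 3, Table 1, the disclosure of allocation and the interaction model together mean that, followed as written, the plan would treat two post-allocation ratings as moderators. That conclusion rests on the text alone.

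The size is conditional. False interactions run from about 5% to about 30%, against about 5% for a baseline moderator, and the upper end needs a rating that tracks prognosis at .7 in one arm and not at all in the other. The documents give no correlations, so these rates show what is possible and do not predict what this trial will find. It would be too strong to infer that every interaction with these ratings will be spurious.

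The mediator point is secondary. The content overlap is real if the Global score includes Restraint, which is assumed, and it matters only if treatment shifts the EDE. Taking the mediator earlier would help with temporal order but would not remove the overlap.

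**What to change.** 1. In hypothesis 3 and Data analysis, limit moderators to the five factors with baseline measures: psychiatric comorbidity, obsessionality, personality disturbance, parent psychopathology and parental criticism.
2. Keep expectancy and therapeutic relationship as post-allocation predictors or process variables, and describe them as such. Report adolescent relationship scores by arm and do not pool them across arms.
3. Add a sensitivity mediation analysis for restraint on an outcome that excludes it: the ≥95% EBW criterion alone, or the mean of the other three EDE subscales.

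This takes rewording and minor programming, with no new data. The cost is that two factors leave the moderator list. The outcomes in item 3 are narrower than full remission, so they supplement the planned mediation analysis and do not replace it.
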